### Measurement of results, primary and secondary outcomes

Outcome measures will be evaluated in several stages: at the beginning (before the beginning of interventions) and at the end of 10 sessions (subjective interview, pelvic floor muscle assessment, KHQ, Short-Form 6 Dimensions- Brazil, King´s Health Questionnaire for Scoring Algorithm and voiding diary). During the follow-up, the outcomes measures will be evaluated by telephone for 6 months. The economic evaluation will be performed during the 6 months of follow; however, at the 3rd and 6th follow-up assessment, we will apply the KHQ, Short-Form 6 Dimensions—Brazil, King’s Health Questionnaire for Scoring Algorithm, additional to the economic evaluation.

The primary outcomes will be urinary symptoms and impact of UI on quality of life. The secondary outcomes will be health cost analysis and PFM function. The impact of UI will be carried out using the KHQ and Short-Form 6 Dimensions—Brazil (SF-6D) questionnaires. Urinary symptoms will be assessed by the voiding diary that will be given to the participant. Cost analysis will be investigated by questionnaires and the PFM function will be assessed by vaginal palpation and manometry.

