To assess the presence of urinary symptoms, participants will be instructed to complete a 24-h voiding diary. This instrument contains questions related to the urinary habits, such as the information on number of urinations, amount of urine eliminated, and occurrence of urinary loss. In addition, the voiding diary will quantify the use of absorbents, diapers, and linings (if used and the number of changes) [24, 25]. Participants will be encouraged to complete the voiding urinary twice: once at the pre-treatment before the beginning of the intervention and at the end of the treatment (10th session). The results from the voiding diary will be analyzed by urine loss frequency, considering the urinary leakage associated to stress (e.g., coughing, sneezing, physical exercise or household activities).

Health costs related to UI will be assess by two different questionnaires: (i) SF-6D, validated to Brazilian Portuguese by Campolina et al. [26], and (ii) *King´s Health Questionnaire for Scoring Algorithm*, elaborated by Brazier et al. [27]. The SF-6D evaluates items related to functional capacity, global limitation, physical aspects, emotional aspects, social aspects, pain, mental health, and vitality. This questionnaire allows to generate utility indexes (adjusted by years of life) from data of effectiveness used in economic analyzes. The *King´s Health Questionnaire for Scoring Algorithm* is based on specific health measures of UI, which assesses utility based on quality of life with a five-dimensional classification: functional limitation, physical limitation, social limitation, emotions, and sleep. This questionnaire presents a score of validity pointed in 0.62. Both questionnaires have a unique score ranging from 0 to 1 (where 0 represents the worst health status and 1 represents the better health status) [27].

The psychometric properties of the instruments and procedures are present in Table 2.

**Table 2 Tab2:** Psychometric properties of the instruments and procedures

Examination procedure	Description of procedure	Indicator of musculoskeletal dysfunction	Reported psychometric properties
Modified Oxford Scale (MOS)	Vaginal palpation performed by introduce of two fingers inside participant vaginal canal	Subjective evaluation of PFM function	Intra-rater reliability of MOS (Kappa test) [19] Bidigital palpation 0.75 Inter-rater reliability of MOS (Kappa test) Bidigital palpation 0.60

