### Randomization and allocation

Once included, the initial assessments will be carried out before the participants are randomized (1:1:1) into three groups (CG (control group without physiotherapist-guidance booklet related to PFMT), IG 1 (intervention group 1, that will perform PFMT with physiotherapist supervision once a week), and IG2 (intervention group 2, that will perform PFMT + NMES with physiotherapist supervision once a week)), using the electronic system “Randomization Main.” One researcher, who will not be involved into the participants’ recruitment or treatment, will perform the randomization by the electronic system and will maintain the randomization numeric sequence inside opaque envelopes (Fig. 1). After the assessment of the eligibility, one physiotherapist responsible for the application of the interventions will open one sealed opaque envelope (containing the proposed treatment and the code of “Randomization Main”) and will schedule the date to the beginning of treatment as specified by one of the three groups.

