At the interview and physical assessment, the subjective interview record will be applied, which generates qualitative variables that will be presented as frequencies and percentages and quantitative variables that will be presented as minimum value, maximum value, mean, median, and standard deviation. One researcher will perform the vaginal palpation and the manometry assessment, as well as applied SF6-D, KHQ, King´s Health Questionnaire for Scoring Algorithm, health cost analysis form, and 24 h-voiding diary, which will result in quantitative scales that will be presented as minimum value, maximum value, mean, median, and standard deviation.At the end of treatment sessions, vaginal palpation and manometry will be repeated, as well as SF6-D, KHQ, King’s Health Questionnaire for Scoring Algorithm, health cost analysis form, and the 24 h-voiding diary, which will result in quantitative scales that will be presented as minimum value, maximum value, mean, median, and standard deviation.At the 1st to the 6th month of follow-up, the health cost analysis form will be applied, and at the 3rd and 6th month of follow-up, the SF6-D, KHQ, King´s Health Questionnaire for Scoring Algorithm, and health cost analysis form will be completed, which will result in quantitative scales that will be presented as minimum value, maximum value, mean, median, and standard deviation.At the end of the treatment, the ANOVA for repeated measurements will be applied to verify the effects of the three groups and the two stages (pre-treatment and re-assessment after finished the intervention protocol) and the interactions between them according the results related to the vaginal palpation, manometry, SF6-D, KHQ, King´s Health Questionnaire for Scoring Algorithm, health cost analysis form, and 24 h-voiding diary, if the residues present normality. If the residues do not present normality, a non-parametric test will be applied.At the end of the follow-up, the repeated measures ANOVA will be applied to verify the effects of the three groups and the eight stages (pre-treatment, re-assessment after finished the intervention protocol and 1, 2, 3, 4, 5, and 6 months of the follow-up) and the interactions between them considering the SF6-D, KHQ, King’s Health Questionnaire for Scoring Algorithm, health cost analysis form, and 24 h-VD, if the residues present normality. If the residues do not present normality, a non-parametric test will be applied.The cost-utility assessment will be performed by the quality-adjusted life years (QALY), which combines the length and quality of life into a single index number between 0 and 1, where 0 corresponds to a health state judged to be equivalent to death and 1 corresponds to optimal health [35, 36]. To conduct the statistical analysis, the mean between-group cost differences will be corrected for their baseline, and the total costs will be divided by the costs differences for incremental analysis of cost-effectiveness and cost-utility ratios. Subsequently, a deterministic cost-utility value and a probabilistic one will be determined by applying a bootstrapping technique of 5000 interactions and the bias-corrected, in order to compare health costs between groups. The results will be presented with the confidence interval of 95% (95% CI). The likelihood of the cost-effective intervention will be estimated by the cost-effectiveness acceptability curves to compared values other than willingness to pay [37]. The Kaplan-Meier method and the Log-Rank between-group comparison test will be applied in order to assess the sensitivity of the uncertainty of each parameter by assessing the changes in the results in the range of parameter values [38].

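### The economic analysis states a baseline correction for the cost difference but none for the QALY difference, although utility is measured before randomization in every woman, so free precision is given up

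*Protocol article*

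**What the plan says.** In the Statistical analysis plan section, the item on economic methods bases the cost-utility analysis on QALYs. It then sets the one baseline correction named for the economic comparison: "the mean between-group cost differences will be corrected for their baseline". The sentence continues that "the total costs will be divided by the costs differences for incremental analysis of cost-effectiveness and cost-utility ratios". Uncertainty is to be handled by "applying a bootstrapping technique of 5000 interactions and the bias-corrected, in order to compare health costs between groups", followed by acceptability curves. Nowhere does the article state a baseline correction for QALYs or utilities in the economic analysis.

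The utilities come from the SF-6D and the KHQ scoring algorithm, both scored 0 to 1 under Evaluation tools. Of the SF-6D that section says: "This questionnaire allows to generate utility indexes (adjusted by years of life) from data of effectiveness used in economic analyzes". The section on primary and secondary outcomes schedules both instruments "at the beginning (before the beginning of interventions) and at the end of 10 sessions". The Statistical analysis plan repeats them later: "at the 3rd and 6th month of follow-up, the SF6-D, KHQ" and the scoring algorithm are completed then. Under Randomization and allocation, "the initial assessments will be carried out before the participants are randomized (1:1:1) into three groups". The Trial design section specifies simple randomization, so nothing in the design balances baseline utility across arms.

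**The concern.** A cost-utility result has two components, and a baseline correction is stated for only one. The omitted one depends heavily on baseline. If the QALY is the area under the utility curve, baseline utility is part of the outcome and also predicts the later utilities. Women who start higher accumulate more QALYs in any arm.

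Follow-up ends 6 months after a 10-week treatment, so the QALY horizon is under a year and plausible differences are small. An analyst following the text as written would adjust costs, leave QALYs unadjusted, and carry chance imbalance in utility into the effect side of the result. Bootstrapping the unadjusted difference reflects that imbalance in the width of the interval but does not remove it. At stake is the precision of a secondary aim. The KHQ and urine-loss comparisons are not affected.

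**Working it through.** The plan gives no figure for the QALY difference to reproduce. Its only number used here is the size per arm.

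**Inputs from the article**
- Women per arm: 132 / 3 = 44 (Sample size calculation). Less the 4 added for losses, this is 40.
- Utility visits: baseline, end of 10 weeks of treatment, then 3 and 6 months later. In years: 0, 10/52 = 0.192, 0.442, 0.692.

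**Assumptions, not in the article**
- QALY by the trapezoid rule.
- The same utility SD at every visit, 0.08 to 0.15.
- The same correlation r between any two visits, 0.3 to 0.7.

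**Step 1, trapezoid weights**
- Baseline: 0.192/2 = 0.096
- End of treatment: (0.192 + 0.25)/2 = 0.221
- Month 3: 0.250
- Month 6: 0.125
- Total 0.692 year, of which 0.596 falls on the post-baseline visits.

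**Step 2, slope of QALY on baseline utility**

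Slope = 0.096 + r × 0.596.

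**Step 3, variance removed by adjustment**

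In units of SD², the QALY variance is (1 − r) × Σw² + r × (Σw)², with Σw² = 0.1363 and (Σw)² = 0.4793. The share removed is slope² divided by this variance. The standard error falls by 1 − √(1 − share).

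| r | Slope | QALY variance / SD² | Share removed | Fall in SE |
|---|---|---|---|---|
| 0.3 | 0.275 | 0.239 | 0.32 | 17% |
| 0.5 | 0.394 | 0.308 | 0.50 | 30% |
| 0.7 | 0.513 | 0.376 | 0.70 | 45% |

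The share removed does not depend on the SD or on the number of women.

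**Step 4, effect of a chance imbalance**

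The standard error of the baseline difference between two arms is SD × √(2/n). With n = 40 this is 0.08 × 0.2236 = 0.0179 up to 0.15 × 0.2236 = 0.0335. The shift in the unadjusted QALY difference per one standard error is slope × that value:
- Low end: 0.275 × 0.0179 = 0.0049
- Middle (SD 0.12, r = 0.5): 0.394 × 0.0268 = 0.0106
- High end: 0.513 × 0.0335 = 0.0172

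With all 44 per arm the range is 0.0047 to 0.0164.

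**Step 5, scale**

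A utility gain of 0.03, chosen here as a yardstick, present at all three post-baseline visits gives 0.03 × 0.596 = 0.0179 QALY. A baseline imbalance of the same 0.03 shifts the unadjusted difference by 0.03 × 0.275 = 0.008 to 0.03 × 0.513 = 0.015 QALY. At 44 per arm, the chance that a given pair of arms differs by more than 0.03 at baseline is 8% (SD 0.08) to 35% (SD 0.15).

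**The case against.** The strongest counter-argument is that the article is silent on QALY adjustment rather than opposed to it. It does not say how the QALY is built or which utility instrument feeds it, and such detail may sit in a fuller plan. The sentence is also badly formed: read literally, its ratio has no effect term. It is hard to treat its mention of costs as a deliberate exclusion of QALYs. This stands in part. A reader might infer that the investigators decided against adjusting QALYs, and the text does not support that. What remains is that the article does state a baseline correction and attaches it to costs alone.

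Second, randomization protects the comparison. This is right. A reader might infer that the unadjusted cost-utility result would be biased or invalid. It would not be: under 1:1:1 randomization the difference is correct on average, and the bootstrap interval reflects chance imbalance. The loss is of precision, together with the realised imbalance in this one trial. The same argument would make the stated cost correction unnecessary, yet the plan includes it.

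Third, the size is assumed. That also stands. SD, correlation, QALY construction and the 0.03 yardstick are not in the article. The direction holds for any positive correlation between visits. No claim is made about power, because no significance test of QALYs is stated. None is made about the shape of the acceptability curve, which also depends on cost variance and the cost–QALY correlation.

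Finally, it might be said that the repeated-measures ANOVA already deals with baseline. It compares questionnaire scores by group and stage, and does not produce the incremental QALY needed for the cost-utility analysis.

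**Conclusion.** The point holds as a free improvement, not as a fault that invalidates the analysis. The stated baseline correction covers costs only, while the data to correct QALYs are already collected before randomization. Under an area-under-the-curve QALY and equal between-visit correlation of 0.3 to 0.7, adjustment would cut the variance of the incremental QALY by about 32% to 70%. With utility SD 0.08 to 0.15 and 40 women per arm, a one-standard-error imbalance would otherwise move it by about 0.005 to 0.017 QALY.

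The ratio wording has to be repaired at the same time. As written it divides total costs by cost differences, so a baseline-adjusted QALY difference would enter no stated ratio.

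**What to change.** Revise the economic item of the Statistical analysis plan section in two places.

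1. State that the between-group differences in costs and in QALYs will be corrected for baseline cost and baseline utility respectively, using the same utility instrument as the QALY. Estimate each contrast (IG1 versus CG, IG2 versus CG, IG2 versus IG1) by regressing cost on arm and baseline cost, and QALY on arm and baseline utility. Fit both regressions within each of the 5000 bootstrap replicates.
2. Replace the ratio wording. For the cost-utility ratio, the baseline-adjusted cost difference is divided by the baseline-adjusted QALY difference.

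The cost is a short change of wording and one covariate in the bootstrap code. It needs no further data, visits or participants, and is best done before any analysis by group.

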Data related to the economic analysis in health costs may be considered a relevant tool to be evaluated during SUI treatment. Studies that aim to identify the cost-effectiveness and cost-utility of a specific intervention may be used by governments’ institutions during the decision-making regarding the best evidence-based intervention that may correct the public health problems according their direct finite resources [13]. In Brazil, there are no estimates regarding annual expenses for the treatment of UI. However, it is known that more than $16 billion are spent on UI treatment in the USA annually [14]. It is expected that the economic analysis may affect directly the development of new guidelines related to the clinical practice of health professionals who treat women with SUI.

Therefore, the primary aim of this study is to evaluate the effects of intravaginal NMES associated with the PFMT protocol on urinary loss and quality of life in women with SUI. The secondary aim is to evaluate the cost-effectiveness and cost-utility and pelvic floor muscle in women with SUI.

The hypothesis of the study is that both treatments (NMES associated with PFMT and PFMT) will present good effectiveness; however, considering greater cost-effectiveness, PFMT will be the best option.

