Manometry	Peritron^TM^ manometer: insertion of a probe into the vaginal canal of participant	Objective evaluation of PFM function	Intra-rater reliability 0.96 [28]
KHQ	Score variating 0 to 100 = the higher the score, the worse the quality of life	Impact of urinary loss	Internal consistency 0.87 [17] Reproducibility: evaluated by Pearson’s coefficient for all domains [29] (listed below): Perception of health 0.36 Impact of incontinence 0.60 Limitations of daily activities 0.75 Physical limitation 0.74 Social limitation personal relationship 0.82 Emotions 0.76 Sleep/energy 0.62 Severity measures 0.71 Minimum relevant clinical difference: 5 points [23] Responsiveness: evaluated by Cronbach’s alpha for all domains [30] (listed below): General health perception − 0.76 Impact of incontinence − 1.94 Role limitations − 1.50 Physical limitations − 1.49 Social limitations − 1.33 Personal relationships − 0.76 Emotions − 1.44 Sleep/energy − 0.86 Severity measures − 2.40
SF-6D	Score between 0 to 100 = the higher the score, the better the health status	Quality of life that constructed data about effectiveness, used in economic analyzes	Internal consistency: – Reproducibility intra-rater: evaluated by Pearson’s correlation coefficient for all domains [31] (listed below): Functional capacity 0.8 Physical aspects 0.63 Social aspects 0.75 Emotional aspects 0.44 Pain 0.54 Vitality 0.65 Mental health 0.69 General health status 0.84 Specificity: – Minimum relevant clinical difference: – Responsiveness: 0.404 (performed in women with postoperative pelvic organ prolapse; the value of the total score was used to identify the result of responsiveness through the ANOVA test) [32]
King’s Health Questionnaire for Scoring Algorithm	Score: 0 = worst health status 1 = better health status	Health measures of UI	Internal consistency: – Reproducibility: – Specificity: – Minimizes relevant click difference: – Responsiveness: evaluated by standardized response mean (SRM) for all domains (listed below). The SRM is a version of the effect size that divides the mean change by the standard deviation of the change [27]: Role 0.56 Physical 0.51 Social 0.39 Personal 0.33 Emotions 0.37 Sleep 0.41 Severity 0.50 Valid: –

MOS, Modified Oxford Scale; PFM, pelvic floor muscle; KHQ, King’s Health Questionnaire; SF-6D, Short-Form 6 Dimensions—Brazil; UI, urinary incontinence

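### The incremental cost ratios are defined as cost over cost, with no health effect, and a time-to-event method is named for parameter sensitivity

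*Protocol article*

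**What the plan says.** The economic question is a declared objective. The Introduction states: "The secondary aim is to evaluate the cost-effectiveness and cost-utility". The Abstract says that incremental cost-effectiveness and cost-utility ratios will be used, but gives no formula.

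The only operational definition is in the last item of the detailed list under Statistical analysis plan:

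- On the unit of effect for cost-utility: "The cost-utility assessment will be performed by the quality-adjusted life years (QALY").
- On costs: "the mean between-group cost differences will be corrected for their baseline".
- On the ratios: "the total costs will be divided by the costs differences for incremental analysis of cost-effectiveness and cost-utility ratios".
- On uncertainty, a bias-corrected bootstrap with 5000 replicates and 95% intervals, whose stated purpose is to compare health costs between groups, followed by acceptability curves.
- On parameter sensitivity: "The Kaplan-Meier method and the Log-Rank between-group comparison test will be applied in order to assess the sensitivity of the uncertainty of each parameter". The sentence goes on to say that the aim is to see how results change over the range of parameter values.

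On the utility source, Evaluation tools says of the SF-6D: "This questionnaire allows to generate utility indexes (adjusted by years of life) from data of effectiveness used in economic analyzes". It says of the SF-6D and the KHQ scoring algorithm together: "Both questionnaires have a unique score ranging from 0 to 1". The SF-6D row of Table 2 in the same section says: "Score between 0 to 100 = the higher the score, the better the health status".

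**The concern.** An incremental ratio tells a payer what one more unit of health costs when moving from one option to another. It needs a difference in cost above the line and a difference in effect below it. The written rule has no effect term, so it cannot distinguish an arm that improves health from one that worsens it, and it cannot be set against a willingness-to-pay value.

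The sensitivity method has a separate problem. Kaplan-Meier curves and the log-rank test compare times to an event. Varying a unit price or a utility over a range is a different operation, and those methods do not perform it.

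At stake is the economic conclusion. The Introduction expects PFMT alone to be the better option on cost-effectiveness, whereas the Discussion paragraph of the Abstract expects PFMT plus NMES to be best once effectiveness, cost-effectiveness and cost-utility are considered. A correctly defined comparison of IG2 with IG1 is what could settle this, and the Introduction expects the economic results to influence guidelines.

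**Working it through.** The article reports no cost, QALY or ratio figure to reproduce. The check is therefore algebraic, with an illustration on assumed values.

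**1. The two definitions side by side.** Let C1 and C0 be the mean costs in the dearer and cheaper arm, and E1 and E0 the mean effects.

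- As written: C1/(C1 − C0), or (C1 + C0)/(C1 − C0) if total cost means the sum over both arms. Currency cancels and no E appears.
- Standard: (C1 − C0)/(E1 − E0), in currency per unit of effect or per QALY.

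**2. Illustration.** Assume C0 = 500 and C1 = 800, so the cost difference is 300. These values are not in the documents.

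| QALY difference | Written ratio (C1 only) | Written ratio (sum) | Standard ratio |
|---|---|---|---|
| 0.05 | 800/300 = 2.67 | 1300/300 = 4.33 | 300/0.05 = 6,000 per QALY |
| 0.02 | 2.67 | 4.33 | 300/0.02 = 15,000 per QALY |
| 0 | 2.67 | 4.33 | undefined |
| −0.02 | 2.67 | 4.33 | −15,000: dearer and worse, so dominated |

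The particular values do not matter. Under either reading of total cost, the written quantity does not move with the effect. It also grows without limit as the cost difference approaches zero: with costs of 510 and 500 it would be 510/10 = 51.

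**3. What this does to the bootstrap and the acceptability curve.** The probability that an option is cost-effective at willingness to pay λ is the share of replicates in which λ(E1 − E0) − (C1 − C0) exceeds zero. Each replicate must carry an effect difference as well as a cost difference. The plan states the bootstrap's purpose in terms of costs only, and its sentence on the curves speaks of values other than willingness to pay, although willingness to pay is the axis of such a curve.

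**4. Sensitivity method against the outcomes.** Measurement of results, primary and secondary outcomes lists urinary symptoms and quality-of-life impact as primary, and costs and pelvic floor muscle function as secondary. None is a time to an event, and no event, time origin or censoring rule is defined anywhere. Evaluation tools does describe inputs that could be varied: prices come from the public health system's list, the professional council's fees and the average of three private budgets, and two utility instruments are used. Kaplan-Meier and log-rank have no place to put these.

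**5. SF-6D range.** The text of Evaluation tools gives 0 to 1, and Table 2 gives 0 to 100. Both cannot describe the same score.

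**The case against.** The strongest reply is that this is a slip of drafting or translation. The Abstract names the right quantities. The same paragraph names QALYs, a deterministic and a probabilistic cost-utility value, a bootstrap and acceptability curves, and a cost-over-cost figure would clash with that QALY basis. The sensitivity sentence also states a sensible aim, with the wrong technique attached. All of this is fair and limits the size of the point. It does not remove it, because the faulty sentence is the only formula given and nothing in the article corrects it.

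Several stronger readings are tempting but not supported:

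- *That the plan has no valid way to express uncertainty.* It has two, and both work once the ratio is defined.
- *That QALYs will be mis-scaled.* The plan says a QALY combines length and quality of life, so time weighting is intended despite the loose remark about a 0-to-1 index. No passage plans to enter 0-to-100 scores as utilities.
- *That mean costs will not be compared, because the cost form is also listed under ANOVA with a non-parametric fallback.* The bootstrap is planned for that comparison.
- *That omitting a baseline adjustment for utility is an error.* The article is silent on it, and a fuller plan may cover it.

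The objection is also right that the primary outcomes, sample size, randomisation and data collection are untouched.

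**Conclusion.** The concern holds in two parts, plus one minor inconsistency. The ratio rule as written contains no health effect, so it yields neither a cost-effectiveness nor a cost-utility ratio. The method named for parameter sensitivity cannot do that job in a trial without a time-to-event outcome. The SF-6D range is stated in two incompatible ways.

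Followed literally, these instructions leave the secondary economic aim unanswered. The reach of the problem ends there. The first two conclusions rest on the form of the formula and on the list of outcomes, not on assumed data. The costs and QALY differences in the illustration are invented and show only that the written ratio does not respond to effect. The wording may well be a slip, but it should be corrected before the economic data are analysed, so that the definition is not chosen after the results are known.

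**What to change.** Rewrite the economic item of the Statistical analysis plan as follows.

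- **Ratio.** Difference in mean cost divided by difference in mean effect.
- **Effect for cost-effectiveness.** Name one clinical measure, for example stress leakage episodes or one specified KHQ domain. Evaluation tools schedules the voiding diary only before treatment and at the tenth session, whereas the KHQ is also planned at months 3 and 6, so the choice should match the horizon.
- **Effect for cost-utility.** QALYs as the area under the 0-to-1 utility curve, using the visits already planned (baseline, end of treatment, months 3 and 6): the sum over intervals of the mean of the two adjacent utilities multiplied by the interval in years. State one horizon. The outcomes section places the economic evaluation in the 6 months of follow-up, while the analysis section also collects the cost form at baseline and end of treatment.
- **Three arms.** Order them by mean cost, remove dominated options and compare each remaining one with the next. Report IG2 versus IG1 explicitly.
- **Sampling uncertainty.** Keep the 5000 replicates, but resample patients so that cost and effect stay paired. Plot acceptability curves across a range of willingness-to-pay values.
- **Parameter uncertainty.** Replace Kaplan-Meier and log-rank with one-way or probabilistic sensitivity analysis over stated ranges of unit prices (public tariff, professional fee, private budgets) and over the utility instrument.
- **Table 2.** Reconcile the SF-6D range with the text.

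Adjusting QALYs for baseline utility, which is already collected, would be a worthwhile optional improvement.

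The cost is one rewritten paragraph, one table cell and a little more analysis work. No new data are needed.
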